Patients who have a history of previous failed treatment with memantine will not be entered. No medication changes should have occurred in the 7 days preceding trial commencement.

No other restrictions are placed on other prior or concomitant interventions. A list of all prior medications (& doses) will be obtained as part of baseline data collection.

- - 1. **Adverse Events**

Adverse Events will be managed by the Principal Investigator and Co-Director in line with the European Commission document ‘Detailed guidance on the collection, verification and presentation of adverse reaction reports arising from clinical trials on medicinal products for human use’ (Revision 1, 26th April 2004; Document ENTR/CT 3; <http://pharmacos.eudra.org/F2/pharmacos/new.htm>).

Serious Adverse Events are defined here as:

1. **Serious Adverse Events** – those which are fatal, life threatening, disabling or require hospitalisation or prolongation of hospitalisation. All deaths whether thought to be related to the trial intervention or not should be reported as serious adverse events.

1. **Unexpected Adverse Events** – those that would not be expected among elderly patients with AD (See known side effects in BNF).

If any patient suffers an event that fulfils these criteria, a Serious Adverse Event Form should be completed and faxed to the Principal Investigator **within 24 hours of the event being known.** The original form should be stored in the Investigator File and a copy placed in the patient’s source notes.

A trial (/annual) serious adverse events report will be compiled by the Principal Investigator and sent to the LREC. Serious Unexpected Adverse Events, in addition, will be reported immediately to the TSC .

Expedited reporting is required for all suspected adverse reactions that are both serious and unexpected. Fatal or life-threatening SUSARs should be reported to the LREC and the MHRA as soon as possible but no later than 7 calendar days after the sponsor has knowledge of the minimum criteria for expedited reporting. All other SUSARs and safety issues should be reported to the LREC and the MHRA as soon as possible but no later than 15 calendar days after the sponsor has first knowledge of the minimum criteria for expedited reporting.

Expedited reporting is not required for reactions which are serious but expected and for non-serious adverse reactions whether expected or not. Non-serious adverse events should be recorded using the Adverse Event Form.

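### The serious adverse event definition in section 6.5.8 includes unexpected events of any severity, so a non-serious unexpected event is sent to two different forms

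*Protocol*

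**What the plan says.** The text is in section 6.5.8 (Adverse Events). The lead-in is "Serious Adverse Events are defined here as", and two labelled items follow it.

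- The first, labelled as serious events, covers "those which are fatal, life threatening, disabling or require hospitalisation or prolongation of hospitalisation". It adds that every death is to be reported as serious, whether or not it is thought related to treatment.
- The second, labelled as unexpected events, covers "those that would not be expected among elderly patients with AD (See known side effects in BNF". It sets no condition on seriousness.

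The form requirement comes directly after the list: "If any patient suffers an event that fulfils these criteria, a Serious Adverse Event Form should be completed and faxed to the Principal Investigator". The time limit is 24 hours from awareness of the event. The sentence does not say which item, or whether one item or both, triggers the form.

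The section ends with the opposite instruction for events that are not serious: "Non-serious adverse events should be recorded using the Adverse Event Form". Section 6.6 (Unblinding Reporting) repeats this routing when a code break is due to a non-serious event.

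Two outputs use the classification. One is the trial or annual report: a "serious adverse events report will be compiled by the Principal Investigator and sent to the LREC". The other is Steering Committee oversight: "Serious Unexpected Adverse Events, in addition, will be reported immediately to the TSC".

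**The concern.** Seriousness and expectedness are different attributes of an event. Seriousness decides whether an event is a serious adverse event. Expectedness then decides, among serious suspected reactions, which need expedited reporting. Listing unexpected events under the definition of a serious event merges the two. Taken literally, a mild and transient symptom that is not expected in elderly patients with Alzheimer's disease becomes a serious adverse event, although the last sentence of the same section says it is not recorded that way.

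The trial recruits through several trusts, and research doctors or CSOs carry out its assessments. One site may follow the list and another the closing sentence. The number of serious events would then depend partly on who read the section and how. Investigating adverse effects is a stated secondary objective and safety is assessed only descriptively, so the counts carry the interpretation with no formal comparison behind them.

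**Working it through.** The protocol gives no figure on this point, so there is none to reproduce. The check is to route each kind of event through the two instructions in section 6.5.8.

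| Event | List plus form requirement | Closing sentence | Result |
| --- | --- | --- | --- |
| Serious, expected | Meets item 1: SAE form | Does not apply | Consistent |
| Serious, unexpected | Meets items 1 and 2: SAE form | Does not apply | Consistent |
| Non-serious, expected | Meets neither item: no SAE form | AE form | Consistent |
| Non-serious, unexpected | Meets item 2: SAE form within 24 hours | AE form | Conflict |

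Only the last row fails.

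One way out would be to treat serious as a defined term that includes item 2, so that an unexpected event is never non-serious. The section's own later wording rules this out: "Expedited reporting is not required for reactions which are serious but expected and for non-serious adverse reactions whether expected or not". That sentence presupposes non-serious reactions that are unexpected. The rule for expedited reporting likewise requires a reaction to be serious and also unexpected, which would be redundant if unexpectedness alone made an event serious.

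The forms in Appendix 4 do not settle it. The first question on the SAE form offers tick boxes for the seriousness criteria and an open box for other reasons, with none for unexpectedness. A site following item 2 could use the open box. The AE recording form has free-text lines that accept the same event.

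The effect on the count can be written in symbols. Let S be the number of events meeting item 1, and U the number of non-serious unexpected events. If every site follows the closing sentence, the serious count is S. If every site follows the list, it is S + U. With a mixture it lies between the two, so the largest relative inflation is U/S. The protocol gives neither S nor U, so no numerical range can be supported.

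**The case against.** The strongest reply is that this is loose drafting with little consequence, and much of that stands.

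- The literal reading over-reports. A mild unexpected event would reach the Principal Investigator sooner and on a fuller form, so no safety signal is lost. The Steering Committee's terms of reference cover unexpected reactions as well as serious events, so seeing both fits its remit.
- The seriousness boxes on the SAE form would let the Principal Investigator, who receives the forms and compiles the ethics committee report, separate most misfiled events. The open box leaves some uncertainty.
- Section 6.7.5 tabulates adverse event frequencies by group and plans no statistical comparison of safety parameters. It names no comparison of serious events by arm.
- The contents page lists a subsection on adverse event reporting at the start of section 6.6. Its text is not in the copy available here, and it may clarify the routing. If so, the conflict in 6.5.8 would still need correcting, but sites would have somewhere to resolve it.

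A reader might also infer that an event must satisfy both items, so that serious but expected events miss the SAE form and the 24-hour route. The protocol does not support that. The first item is a complete definition under its own label. Deaths are serious without any test of expectedness. Serious unexpected events go to the Steering Committee as an additional step, which implies that serious expected events are already being reported as serious. Section 6.6 requires the SAE form for a code break due to a serious event, again without regard to expectedness.

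A reader might further infer that counts could not be pooled or compared by arm at all. That goes too far, given the seriousness boxes and the absence of a planned comparison.

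**Conclusion.** The definition is wrong as written and contradicts the rest of its own section. The defect is confined to non-serious unexpected events, which have two incompatible routes. The consequence is that the serious event count in the ethics committee report and before the Steering Committee may be inflated, or may vary by site. That sites will in fact diverge is an inference from the text, not something the protocol shows.

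Expedited reporting is sound, because its rule correctly requires both attributes. The handling of serious expected events and the efficacy analysis are untouched. The size is unknown without event rates. The correction is worth making because it is cheap and the count is part of the trial's safety oversight; it does not call the design into question.

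**What to change.** In section 6.5.8, let the definition of a serious adverse event consist of the first item alone, and tie the SAE form and the 24-hour requirement to it. Move unexpectedness to a separate definition, recorded as its own judgement and used only for expedited reporting and for immediate notification of the Steering Committee. Extend the closing sentence to say that non-serious events go on the AE form whether expected or not. Check that the adverse event reporting subsection of 6.6 uses the same terms.

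The cost is rewording one list and one sentence, plus re-coding any non-serious events already filed as serious. The tick boxes on the SAE form should identify most of these; entries under the open box need individual review.

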**Randomisation**

Memantine group

Placebo group

2 week assessment

4+ 6 week assessment

12 week assessment

Rescue treatment as per trust protocol up to **week 3**

- - 1. **Determining Response to Memantine**

Response to memantine will be determined as follows:

- - 1. Reduction in Agitation as measured by the CMAI will be the primary outcome measure. Thus it may be expected that if Memantine is effective in treating the agitation symptoms associated with AD, then more patients will remain in the trial in the treatment group than the placebo group and there will be a reduction in Agitation score on the CMAI.
    2. Secondary outcome measures include improvement in Neuropsychiatric inventory (NPI), Clinical Global Impression (CGI), Severe Impairment Battery (SIB), Quality of Life (QOL-AD) co-prescribed medications, number of recorded incidents of aggression, and number of occasions rescue treatment utilised.

All measures will be assessed at baseline.

The following scales will be completed for each patient at 2,4, 6 and 12 weeks;

a)Cohen-Mansfield Agitation Inventory

b)Mini-Mental State Examination

c)Clinical Global Impression of Change

The NPI , SIB and QOL-AD will be measured at 6 and 12 weeks.

We will allow follow up assessments to have a 7 days window from randomisation. Baseline assessments will occur prior to randomisation and follow up assessments after randomisation.

.

- - 1. **Unblinding Reporting**

Unblinding is defined here as anyone except the randomiser who is able to identify which group (active drug or placebo) a patient has been assigned to.

If either of the above are fulfilled, a Codebreak Form should be completed **as soon as possible** after the blind has been broken by the person for whom the blind has been broken. The form should be faxed to the Chief investigator and the original kept in a locked filing cabinet.

If the codebreak is due to a Serious Adverse Event, the Serious Adverse Event Form should be completed and processed in the usual way. If the codebreak is due to a non-serious adverse event, the Adverse Event Form should be completed and filed in the source notes.

- 1. **Statistical Methods**

For a two-tailed test with power of 80% and statistical significance of 5% the number of patients necessary in each of two equally sized study groups is 82 (164 subjects in total) which includes a 20% attrition rate. In order to calculate the sample size, a repeated measures approach has been adopted, taking advantage of the fact that, for each patient, there will be observations at 4 different time points in the treatment period, in addition to the baseline observation. A simple covariance structure (stationary first order autoregressive) for the observations in the treatment period has been assumed (meaning that an observation for a patient at any time point is most closely associated with the immediately preceding observation for that patient). This is a weaker assumption than that of compound symmetry (the correlation between observations for a patient at different time points is the same, whatever the difference in time). Whilst this would lead to a smaller sample size, the scientific basis of the stronger assumption would be more difficult to justify.

6.7.3 Hypothesis of interest

The minimum clinically significant mean change difference is 6 points measured on the CMAI scale between the Memantine and placebo groups, as observed after 6 weeks of treatment.

6.7.4 Study populations

ITT population: All patients, who were randomised, have taken at least one dose of study drug and have valid CMAI scores both at baseline and after 6 weeks of treatment (with application of LOCF in the latter case, where necessary).

Safety Population: All patients, who were randomised and have taken at least one dose of study drug.

6.7.5 Statistical Methods

An analysis of covariance of the post-randomisation mean CMAI scores will be carried out, with the pre-randomisation values (baseline values) used as covariate for each patient, in order to provide a comparison between the treatment groups. In this repeated measures analysis, a stationary, first order autoregressive covariance structure will be assumed for the observations in the treatment period. This analysis and its underlying assumptions are consistent with the assumptions used in the sample size calculations, to achieve 80% power. As a standard part of the statistical analysis, the underlying assumptions will be checked.

Treatment group mean comparisons with baseline values as covariates will be repeated, as secondary analyses, for assessments after 2 weeks, 4 week, 6 weeks and 12 weeks of treatment

The secondary efficacy parameters will be assessed as follows:

- the mean percent change measured on Neuropsychiatric Inventory (NPI) from baseline to endpoint after 6 weeks and 12 weeks,

- the mean percent change measured on Clinical Global Impression (CGI) from baseline to endpoint after 6 weeks and 12 weeks of treatment,
- the mean percent change measured on Severe Impairment Battery (SIB) from baseline to endpoint after 6 weeks and 12 weeks of treatment,

- the mean percent change measured on Quality of Life (QoL-AD) from baseline to endpoint after 6 weeks and 12 weeks of treatment,

These parameters will be analysed in a manner similar to that for the CMAI scores.

The difference between the Memantine and placebo group in the proportion of responders (patients achieving at least 50% reduction in their total CMAI score) will be analysed via a logistic regression model, with terms for treatment and baseline CMAI-score. Odds ratio estimates with their 95% confidence intervals will also be derived by SAS PROC GENMOD and/or PROC LOGISTIC, to measure the treatment effect.

The difference in the number of recorded incidents of aggression will be analysed with a logistic regression model containing the term for treatment only.

Demographic characteristics, clinical characteristics and co-described psychotropic medication will be summarised by frequency and percentage (discrete variables); mean, standard deviation, minimum, maximum values and 95% confidence interval for the mean (normally distributed continuous variables); median, minimum and maximum values (non- normally distributed continuous variables).

Safety and tolerability will be assessed by descriptive statistical methods. Frequency of adverse events will be tabulated by treatment groups. No statistical comparisons will be performed for the safety parameters.

- - 1. **Planned Recruitment Rate**

Recruitment is expected to start on 3d January 2007. Randomisation is expected to start on 3RD January 2007. Recruitment is planned to finish October 2009. We have assumed that the recruitment rate will be linear across the trial period. The actual recruitment and randomisation targets are given below.

| Month | Recruitment Target | Cumulative target |
| --- | --- | --- |
| 10/2007  11/2007  12/2007  01/2008  02/2008  03/2008  04/2008  05/2008  06/2008  07/2008  08/2008  10/2008  11/2008  12/2008  01/2009  02/2009  03/2009  04/2009  05/2009  06/2009  07/2009  08/2009 | 4  4  8  8  8  8  8  8  8  8  8  8  8  8  8  8  8  8  8  8  8  4 | 4  8  16  24  32  40  48  56  64  72  80  88  96  104  112  120  128  136  144  152  160  164 |
| Total | 164 | 164 |

- - 1. **Analysis Plan**

The final analysis plan will be determined in consultation with the statistician. We will summarise the change in CMAI score from baseline to 6 weeks using mean(sd). The main analysis will be a 2-group (memantine vs placebo) comparison for this variable. We will perform analysis on both LOCF and OC data,
 A 2-sample t-test, which is equivalent to a two-way analysis of variance. We will involve standard survival analysis for remaining in trial and between-group ANOVA for clinical measures. Secondary outcomes will be examined.

1. **Data Management**

A data management protocol will be written to cover laptop security and use; anti-virus software; the handling of personal information; data transfer; data collation, cleaning and verification; data back ups; the data query procedure; and data archiving.

- 1. **Access to Source Data / Documents**

Source notes document each contact (personal, telephone or written) with patients, their carers, family or associated health care professionals (e.g. neurologists, GP’s). They include the case report forms used to record the baseline assessments and follow-up assessments as well as basic details on the patient, GP and relative, eligibility assessments and logs of capacity assessments, consent / assent, blood taking and transport, trial code allocation, adverse events, unblinding and data queries. They are specific to the trial and should not be confused with patient’s case notes. Each entry into the source notes should be traceable, signed and dated.

All personal information collected on MAGD trial participants and on potential participants will be treated as confidential information and will be handled according to guidelines set out in this document and in accordance with the terms of the Data Protection Act 1998. All electronic files containing personal information will be held only on password-protected computers. The computers themselves will be kept securely. Source notes will be kept in a locked office.

Trial Identification Numbers will be used in all correspondence; names will not be used in any data transmissions or correspondence except in those to the patient’s carer or clinicians.

In accordance with Good Clinical Practice guidelines, the MAGD Investigators will permit trial-related monitoring and audits providing direct access to source data documents.

The source notes will be retained on site until at least 10 years after the last publication is released for this trial. The source notes will be kept separate from general medical notes to reduce the likelihood of the notes being destroyed in error.

- 1. **Data Handling & Record Keeping**

The primary objective of good data handling and record keeping is to ensure that data collected on participants in the trial are accurate and complete and unbiased with respect to the trial intervention allocation.

Paper copies of all the relevant assessments will be held in the source notes. The information contained on them will be entered into the trial databases as soon as possible. The paper copies will be held as back-up.

An audit trail will be produced to ensure that data can be traced throughout the trial.

- 1. **Data Quality Control & Assurance**

The Trial Management Group will monitor the progress of the trial, paying particular attention to recruitment, adherence to the protocol and patient safety.

1. **Ethical & Regulatory Considerations**
   1. **Ethical Conduct of the Trial**

The trial will be conducted in line with the protocol approved by the TSC, and the REC. The TSC will oversee adherence to ethical conduct.

The main potential ethical issue in this study is that the dementia itself may affect the individuals ability to give their informed consent, especially in more severe stages of the illness. Given that this is an effectiveness study it is very desirable that all potential subjects with acute agitation and Alzheimers are included if the impact of the medication is to be ascertained. This is an important issue in this study’s design as compromised capacity and lack of insight may be a source of significant variation (for example compliance).

The trial group has significant experience in the ethical issues raised by obtaining consent for treatment trials in dementia, including severe dementia. One strength of the study is that carers have been involved in feedback on the design through representation on research governance committees and this will continue prior to trial commencement. The methods of obtaining consent and assent follow best quality practice.

Our approach is designed to comply with normal clinical practice, full informed consent will be obtained where possible, if the person with dementia does not have capacity to consent then the assent of the family will be sort and the interviews and recruitment will be completed only if there is no sign of distress in the person with dementia. This is an approach that has been used successfully in trials and other descriptive and evaluative studies.

The researcher/CSO will be trained in obtaining consent. They will also discuss the study with subjects and carers providing information and will obtain consent or assent as described above. Subjects will be given a 7 day period to consider the information given and their willingness to participate.

- 1. **MREC and / or LREC Approval**

Ethics approval has been applied for from the Multi site Research Ethics Committee (MREC).

- 1. **Other Approvals**

Approval has been applied from the Medicine and Health Regulatory Authority (MHRA)

Approval has been received from the East Kents NHS and Social Care Partnership trust R&D Department and East Kent Hospitals Trust.

- 1. **Indemnity / Compensation / Insurance Arrangements**

NHS trust indemnity will be in place.

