Patients will be allocated to one of the two trial arms (ratio 1:1). Once informed consent or assent has been given, baseline assessment completed , the research fellow/CSO will obtain a treatment code for the subject. Patients will be assigned codes consecutively as they enter the trial. The codes will correspond to the pre-randomised medication packs provided by Lundbeck. There will be a sealed envelope for each treatment code containing details of whether the medication pack for that code contains active drug or placebo. Balancing for severity of agitation, staging of dementia and smoking status will be included. Randomisation using the minimisation approach will ensure that equal numbers are entered into each arm of the trial. Patients will be registered for the trial using an internet allocation system.

- - 1. **Blinding & Unblinding**

It is important that blinding is maintained throughout the trial until the database is closed and the data analyses have been performed.

Unblinding will occur in the event of life-threatening change in physical state or need for urgent medical and/or psychiatric intervention as requested by the patient’s treating physician in consultation with the study team and study monitoring committee.

Unblinding in such circumstances will only occur if it is felt that knowledge of the patients medication status will impact on future medical care.

If unblinding occurs accidentally, it is important that the unblinded individual completes an Accidental Codebreak Form (see Appendix4) for each instance of unblinding (copies will be available from the Trial Research Fellow/CSO).

- 1. **Trial Interventions**
     1. **Flowchart**

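### Allocation is to be minimised on dementia stage and smoking, but no analysis model contains either factor; the test is conservative if both matter, and the allocation text needs reconciling

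*Protocol*

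**What the plan says.** **Allocation (protocol section 6.4, method of assigning patients to trial arms).** The ratio is 1:1. On the factors: "Balancing for severity of agitation, staging of dementia and smoking status will be included". On the method: "Randomisation using the minimisation approach will ensure that equal numbers are entered into each arm of the trial". The same paragraph says: "Patients will be assigned codes consecutively as they enter the trial. The codes will correspond to the pre-randomised medication packs provided by Lundbeck". It adds a sealed envelope for each code giving the contents of the pack, and registration through an internet allocation system. The flowchart that opens section 6.4 puts the steps in this order: allocation, treatment code, matching pack.

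**Analysis (sections 6.7.5 and Analysis Plan).**
- CMAI repeated-measures analysis of covariance: "with the pre-randomisation values (baseline values) used as covariate for each patient". No other covariate is named.
- NPI, CGI, SIB and QoL-AD: analysed in a similar manner to CMAI.
- Responder logistic model: "with terms for treatment and baseline CMAI-score".
- Recorded incidents of aggression: logistic model with treatment alone.
- The Analysis Plan subsection at the end of section 6.7 describes the main comparison of CMAI change as a two-sample t-test, with no covariate.

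**Baseline data.** FAST staging appears in the baseline assessment list (section 6.3) and in the Appendix 1 visit checklist. Smoking status is named in neither.

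**The concern.** Minimisation makes the arms more alike on the chosen factors than simple randomisation would. If those factors predict the outcome, the treatment difference varies less from one repetition of the trial to the next. A model that omits them leaves their variance in the residual and reports a standard error larger than the true one. Intervals are then too wide, and some of the precision gained by the allocation is not used.

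This is not a detail left to a statistical analysis plan, because section 6.7.5 itself fixes the model terms.

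A second issue lies upstream. If codes are issued strictly in order of entry and each code already has an arm, entry order decides the arm and the new patient's factors cannot. Read literally, that is a pre-prepared list and not minimisation. Sites, pharmacies and the analyst need to know which procedure applies, because it decides whether the standard-error argument applies at all.

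**Working it through.** **1. The plan's own sample size.** Inputs from section 6.7: SD 16.84, difference 6 points, correlation 0.6 with first-order autoregressive structure, two-sided 5%, power 80%, attrition 20%. The variance factor for the mean of m post-baseline values adjusted for baseline is f = (average correlation among post-baseline values, diagonal included) − (average correlation with baseline)². Patients per arm: n = 2 × 2.802² × 16.84² × f / 6².

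- m = 3 (weeks 2, 4, 6): f = 0.680 − 0.392² = 0.526; n = 65.1, so 66; 66/0.8 = 82.5, so 83.
- m = 4 (as stated): f = 0.592 − 0.3264² = 0.4855; n = 60.03, so 61; 61/0.8 = 76.25, so 77.

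The stated 82 per arm is reproduced to within one patient with three visits. Neither calculation has an input for stage or smoking, so the point below does not depend on which was used.

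**2. Effect of omitting stage and smoking under minimisation.** Let R² be the share of residual CMAI variance, after baseline CMAI, that the two factors explain. The protocol gives no figure, so 0% to 15% is an assumed range. Assume that minimisation balances the factors well.

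- Excess in reported standard error = 1/√(1−R²) − 1.
- True type I error of the nominal 5% test = 2 × [1 − Φ(1.96/√(1−R²))].
- Power without the factors = Φ((2.802 − 1.96)/√(1−R²)). The estimate already has the smaller true variance; only its reported standard error is too large.
- Power with the factors = Φ(2.802/√(1−R²) − 1.96).

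| R² (assumed) | Standard error too large by | True type I error | Power without | Power with | Gain (points) |
|---|---|---|---|---|---|
| 0% | 0% | 5.0% | 80.0% | 80.0% | 0 |
| 5% | 2.6% | 4.4% | 80.6% | 82.0% | 1.4 |
| 10% | 5.4% | 3.9% | 81.3% | 84.0% | 2.7 |
| 15% | 8.5% | 3.4% | 81.9% | 86.0% | 4.0 |

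**3. Check by simulation.** Biased-coin minimisation (probability 0.8) on dichotomised baseline CMAI, a three-level stage and smoking; 132 evaluable patients (2 × 66, close to 164 × 0.8); residual variance from the four-visit case above. There were 3,000 null runs and 1,500 runs with a 6-point effect per setting. The stage distribution and a 15% smoking prevalence are assumptions.

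| R² | Type I error, baseline only | Type I error, factors added | Power, baseline only | Power, factors added |
|---|---|---|---|---|
| 0% | 0.056 | 0.054 | 0.83 | 0.83 |
| 5% | 0.041 | 0.046 | 0.82 | 0.84 |
| 20% | 0.028 | 0.049 | 0.85 | 0.91 |
| 40% | 0.016 | 0.055 | 0.89 | 0.96 |

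Monte Carlo error is about 0.4 points for type I error and 1 point for power. The mean estimate stayed within 0.1 points of the true effect in every setting. Direction and size agree with step 2.

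**4. The allocation text.** Minimisation needs the arm to depend on the new patient's factors. Consecutive codes tied to pre-randomised packs make it depend on entry order. The flowchart and the internet system allow the two to be joined: the system chooses the arm, then releases a code of that arm. Codes would then not run consecutively across all patients. The conflict therefore rests mainly on that one word.

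**The case against.** **The factors may not be prognostic.** Nothing in the protocol says that stage or smoking predicts CMAI once baseline CMAI is in the model. If they do not, nothing is gained; the 0% rows show it. This stands and is why the range starts at zero.

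**The gain is easily overstated.** A reader might compare the adjusted power of 82%, 84% or 86% with 80% and claim 2, 4 or 6 points. That is the wrong comparator: with effective minimisation the unadjusted analysis already has 80.6%, 81.3% or 81.9%.

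**Validity is not threatened.** A reader might infer a biased or anti-conservative primary analysis. The opposite holds: the estimate is unbiased and the error is conservative.

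**Minimisation is not shown to be impossible.** A reader might infer from the pack text that minimisation could not be carried out. The flowchart and the internet system permit a workable reading, so the documents support only a conflict of wording.

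**The two issues are partly alternatives.** If a consecutive list is what is used, stage and smoking are not balanced by design and the standard-error argument falls away. Adjustment is then ordinary covariate adjustment: useful against chance imbalance, but not required for a valid test.

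**Two smaller points stand.** The formulas are for linear models; in the responder model, added covariates change the odds ratio from marginal to conditional and use up events. Smoking may be recorded under medical history, so its absence by name is a listing gap and not proof that it is not collected.

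**Conclusion.** The point holds as a mismatch between the stated design and the stated models. Three factors drive allocation, and two of them, dementia stage and smoking, appear in no model. The incident model and the t-test also lack baseline CMAI.

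The consequence is a modest, conservative loss of precision. For an assumed 0% to 15% of residual variance explained, the reported standard error is 0% to 8.5% too large, and 0 to about 4 points of power are given up. This rests on three conditions: minimisation is really used, it balances the factors well, and the factors predict CMAI beyond baseline. Only the first can be settled from the protocol, and its allocation text leaves that unclear.

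The correction is worth making because it is cheap and needs no extra patients. The allocation wording should be reconciled whichever procedure was intended.

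**What to change.** 1. **Models.** If minimisation is kept, add dementia stage (FAST) and smoking status, in the categories used for minimisation, to the primary CMAI model and the secondary linear models. This costs about 2 to 4 degrees of freedom out of roughly 130, and no patients.
2. **Responder model.** Add the two factors only if the number of responders supports the extra terms, and state that the odds ratio is then conditional on the covariates.
3. **Allocation text.** Rewrite section 6.4 to describe one procedure. If it is minimisation, say that the internet system selects the arm and then issues a pack code of that arm, and remove the statement that codes are consecutive. If packs have been supplied for strictly consecutive use, the change reaches beyond wording to pack numbering, envelopes and stock at the dispensing pharmacies. If the list is what is intended, withdraw the minimisation claim.
4. **Baseline data.** Name smoking status in the baseline list and the Appendix 1 checklist. Minimisation on smoking needs the item in any case.

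Section 6.7 leaves the full analysis strategy to be written before the blind is broken, so the model terms can still be prespecified.
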